## Methods/design

### Overview

The Mechanisms of Change in Psychotherapy (MOP) study is a randomized controlled trial (RCT) where patients diagnosed with MDD are allocated to either CBT or PDT. It is a clinical trial designed to measure the effects of the two treatments, attempting to answer the questions of what works for whom and how. Clinical assessments are conducted at baseline, several times during therapy, at the end of therapy, and at follow-up investigations 1 and 3 years after treatment termination. All treatment sessions are videotaped. The outcome measures comprise a large range of clinical variables enabling studies on process analyses. Potential moderators and mediators from CBT and PDT will be tested in both treatment arms. A qualitative study will be nested within the RCT.

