#### Mediators of change

Does improvement occur through different or similar change processes (mechanisms) in the two treatment modalities?

We will test the following theoretically based hypotheses:In CBT symptom and functional improvement will be mediated by changes in negative automatic thoughts, dysfunctional attitudes, attributional styles, underlying cognitive schemas, and the learning/development of compensatory skills.In PDT symptom and functional improvement will be mediated by improved self-understanding/insight and emotional awareness, less harsh self-view, more adaptive personality functioning, more mature defense mechanisms, and increased reflective functioning.

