### Statistical analysis plan

An causal graph (DAG) of mediation is shown in Fig. 1, with randomized treatment $$A$$ that corresponds to the two treatment groups in MOP, mediator $$M$$, outcome $$Y$$ that corresponds to symptoms of depression, and mediator-outcome confounders $$C$$. The longitudinal nature of the data in MOP, is well suited to assess mediation, in that group assignment can, with certainty temporally precede the mediator which again one can be sure of temporally precedes the outcome, to assure causal effects. Repeated assessments, both on the mediator and symptoms of depression, can be used to generalize the simple setting with one assessment of each. The basic concepts are easiest illustrated in the simple setting. Traditional methods to study mediation have important limitations concerning interactions and non-linearities [9], in contrast to the counterfactual-based approach, which is able to decompose a total effect of treatment on the outcome into indirect effect (through the mediator), and direct effect (direct relative to the mediator), even in the presence of an interaction between treatment and mediator. It can be argued that the interaction term should be included, even if it’s not statistically significant. In order to specify assumptions and identifiability of effects, the following definitions of indirect / direct effects are needed. In general, let $${a}^{*}$$ and $$a$$ be t**w**o levels of treatment, here the two groups of CBT or PDT.

$$CDE\left(m\right)$$: The controlled direct effect expresses how much symptoms of depression would change on average if the mediator where fixed at level $$m$$ uniformly in the whole population, but the treatment group where changed from $${a}^{*}=0$$ to $$a=1$$

$$NDE$$: The natural direct effect expresses how much symptoms of depression would change if the treatment were set at level $$a=1$$ versus level $${a}^{*}=0$$, but for each individual the mediator were kept at the level it would have taken, for that individual, if she had been in the reference group ($${a}^{*}=0$$) (effect of treatment group assignment on symptoms of depression, that would remain if the pathway from treatment to mediator were disabled).

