$$NIE$$: The natural indirect effect expresses how much symptoms of depression would change on average if the treatment group were fixed at $$a=1$$, but the mediator were changed from the level it would take if $${a}^{*}=0$$ to the level it would take if $$a=1$$ (effect of treatment group assignment on symptoms of depression that operates by changing the mediator).

Simple regression models will suffice to estimate the direct and indirect effects above, but some confounding control assumptions are needed. Randomization of treatment group guarantees unbiased estimation of total effect of treatment group on symptoms of depression, but not unbiased estimation of direct / indirect effects [81]. In order to be able to estimate the $$CDE\left(m\right)$$, an assumption of no unmeasured confounding for the mediator—depression relationship is needed (all confounders are measured and controlled for). This is also a necessary assumption to be able to estimate $$\mathrm{NDE}$$ and $$\mathrm{NIE}$$. In addition, no mediator- depression confounder should be affected by treatment group assignment (the dashed arrow in Fig. 2 has to be absent). If such an influence (arrow) is plausible, the natural direct and indirect effects are not identifiable. The controlled direct effect can still be identified with a structural mean model (SMM), and estimated by g-estimation (Vansteelandt 2016).

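### With the arm-by-mediator interaction included, the plan's single natural indirect effect carries only one therapy's mediator slope, which does not fit separate CBT and PDT mediator hypotheses

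*Protocol article*

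**What the plan says.** The Statistical analysis plan section sets up the counterfactual effects for two "levels of treatment, here the two groups of CBT or PDT". Neither therapy is assigned to level 1.

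- **Natural direct effect (NDE).** The mediator is kept where it would have been for the patient "if she had been in the reference group", that is, at level 0.
- **Natural indirect effect (NIE).** It is how far depression "would change on average if the treatment group were fixed at" level 1 while the mediator moves from its level-0 value to its level-1 value. The version with treatment held at level 0 is not defined.
- **Interaction.** "It can be argued that the interaction term should be included", even when it is not significant. This is a preference, not a commitment.
- **Estimation.** "Simple regression models will suffice to estimate the direct and indirect effects above", subject to the confounding assumptions that follow.

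The hypotheses are specific to each arm. Under Mediators of change, the first begins "In CBT symptom and functional improvement will be mediated by changes in negative automatic thoughts, dysfunctional attitudes", and a second list, headed by insight and emotional awareness, is given for PDT. The Overview adds: "Potential moderators and mediators from CBT and PDT will be tested in both treatment arms". No effect measure is attached to that sentence.

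**The concern.** Both arms are active treatments that the investigators expect to be equally effective, so neither is an obvious reference. There are two families of mediators, one for each therapy, but only one indirect effect, tied to whichever arm is coded 1. If the mediator-depression slope differs between therapies, that effect speaks to the slope in one therapy only. A mechanism in the other therapy could appear small in the indirect effect and be reported as a direct effect, meaning one that bypasses the mediator. The usual check that direct and indirect effects add up to the total would not reveal this, because they do add up.

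**Working it through.** The plan gives no figure for a mediated effect, so there is none to reproduce on this point. The 26 and 64 per group under Power analysis do reproduce with a two-sided t-test (25.52 and 63.77, rounded up), but they do not bear on it.

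**Inputs from the plan:** the NDE and NIE definitions, the interaction term and regression estimation. **Assumed inputs, not in the document:** linear models, a mediator difference of 0.5 SD between arms, a slope of 0.5 in the mediator's own therapy, and a slope between 0 and 0.5 in the other. Confounders are left out for clarity, and the plan's confounding assumptions are taken as met.

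**1. Models.** Mediator: E[M | a] = b0 + b1·a. Outcome: E[Y | a, m] = t0 + t1·a + t2·m + t3·a·m. The slope of Y on M is t2 in the arm coded 0 and t2 + t3 in the arm coded 1.

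**2. The plan's pair (treatment held at 1 for the NIE).**
- NIE = E[Y(1, M(1)) − Y(1, M(0))] = (t2 + t3)·b1
- NDE = t1 + t3·b0
- Sum = t1 + t3·b0 + (t2 + t3)·b1, the total effect.

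**3. The other pair (treatment held at 0 for the indirect effect).**
- Indirect = t2·b1
- Matching direct = t1 + t3·(b0 + b1)
- The sum is the same total. The two indirect effects differ by t3·b1, and the two direct effects differ by the same amount in the opposite direction. Swapping the labels turns the plan's NIE into −t2·b1.

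**4. Example, CBT family.** Mediator means are −1.0 in CBT and −0.5 in PDT; slopes are 0.5 in CBT and 0 in PDT; t1 = 0. Code PDT = 1, so b0 = −1.0, b1 = 0.5, t2 = 0.5 and t3 = −0.5.
- Plan's NIE: (0.5 − 0.5) × 0.5 = 0. Plan's NDE: (−0.5) × (−1.0) = 0.50.
- Held at CBT: 0.5 × 0.5 = 0.25. Matching direct: (−0.5) × (−0.5) = 0.25.
- Both pairs sum to 0.50. The discrepancy is t3·b1 = −0.25.

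For the PDT family, take means of 0.5 in CBT and 1.0 in PDT, with slopes of 0 in CBT and −0.5 in PDT:

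| Family | Coding | Plan's NIE | Version with treatment held at the arm coded 0 |
|---|---|---|---|
| CBT | PDT = 1 | 0 | 0.25 |
| CBT | CBT = 1 | −0.25 | 0 |
| PDT | PDT = 1 | −0.25 | 0 |
| PDT | CBT = 1 | 0 | 0.25 |

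Signs follow the direction of the contrast. Under each coding, the family of the arm coded 0 shows nothing in the plan's NIE.

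**5. Range.** For the CBT family with PDT = 1, PDT slopes of 0, 0.25 and 0.5 give NIEs of 0, 0.125 and 0.25. The CBT-held version is 0.25 throughout.

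**6. Simulation** (least squares, 50 per arm, 4000 replicates, slopes 0.5 and 0 in size). With PDT = 1, the mean NIE was 0.002 for the CBT family (0.251 on the CBT slope) and −0.251 for the PDT family. With CBT = 1, it was −0.247 for the CBT family and 0.001 for the PDT family (0.250 on the PDT slope). Direct plus indirect equalled the total in every run.

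**The case against.** The strongest reply is that nothing here is wrong. The definitions are introduced as general concepts in a simple setting, and no coding is fixed. A full analysis plan, not shown, could recode by mediator family or report both versions, and the Overview's sentence on testing in both arms is compatible with that. The interaction is only argued for; without it the slopes are constrained to be equal and the coding does not matter. The two hypotheses do not require unequal slopes: they could both hold if CBT moves cognitions more, PDT moves insight more, and each mediator relates to depression equally in both arms. The slopes and the 0.5 SD are assumed.

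All of this stands as a limit on the point. A reader might infer that one family will always be misjudged, or that the choice of label alone decides whether a mechanism is found. The document supports neither: the first needs one coding for all mediators, the second a slope of exactly zero in the other therapy. Nor would an untreated reference make the distinction harmless, because the two versions differ by t3·b1 whatever the reference is.

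What the reply does not remove is that the article's own analysis section defines one one-sided effect beside two arm-specific hypothesis families, and provides neither the second version nor a coding rule. Dropping the interaction is no escape either, since it assumes equal slopes rather than examining them.

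**Conclusion.** The point holds in a conditional form. If the interaction is fitted and one coding serves all mediators, the plan's NIE judges one of the two families with the other therapy's slope, and t3·b1 is counted as direct effect. Under the assumed values the NIE for that family lies between 0 and 0.25 SD, against 0.25 SD on its own therapy's slope. The discrepancy is therefore between 0.25 SD and zero, and it vanishes when the slopes are equal. The result rests on linear models, on the plan's confounding assumptions and on illustrative values, not trial data. The NIE is a valid quantity and its decomposition is correct. The weakness is its fit to two arm-specific hypothesis families in a comparison of two active treatments. The change should be made, because the present definition can mislead and the remedy is cheap.

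**What to change.** For every mediator, fit the interaction model and report:

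- the indirect effect with treatment held at CBT, with its matching direct effect;
- the indirect effect with treatment held at PDT, with its matching direct effect;
- their difference, t3·b1.

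Use one stated direction of contrast throughout, so that signs are comparable. State in advance that the CBT family is read from the CBT-held version and the PDT family from the PDT-held version.

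State the limit as well: both versions are multiples of b1, so they describe mediation of the difference between arms only, and both are zero when the two therapies move the mediator equally. They do not by themselves show how improvement arises within one therapy.

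The cost is one more line of output per mediator, from the same fitted models and with no new data.

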**Methods:**

One hundred patients with a diagnosis of MDD will be randomized to either CBT or PDT. Patients will be treated over 28 weeks with either CBT (one weekly session over 16 weeks and three monthly booster sessions) or PDT (one weekly session over 28 weeks). The patients will be evaluated at baseline, during the course of therapy, at the end of therapy, and at follow-up investigations 1 and 3 years post treatment. A large range of patient and observer rated questionnaires (specific preselected putative moderators and mediators) are included.

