## Intervention: CBT compared to PDT for treatment of patients with MDE

### Therapists

The psychotherapy with CBT and PDT are conducted by therapists from Nydalen and Vinderen psychiatric outpatient clinic, who have completed a minimum of two-year training in CBT and PDT. In addition, all therapists receive specific training in the CBT and PDT study manuals prior to commencing as therapists in the study. All treatment sessions are videotaped and independent psychiatrists will carry out assessment of treatment fidelity on a selection of random tapes.

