### Power analysis

With reference to a t-test comparison of two independent groups (of equal size) as the total effect, a sample size (each group) of 26 / 64 would provide 80% power (significance level of 5%) to detect a difference of a large (0.8) / medium (0.5) effect size, respectively. With respect to power and sample-size calculations for mediation analysis, current literature is somewhat limited [81]. Kenny and Judd [51] showed that in many settings, power to detect indirect effects is higher than that for total effects, and power to detect direct effects is less than that for total effects. In the present study, this should imply a reasonable power for direct effects, to a less extent indirect effects and even less for moderators. However, the Personalized Advantage Index (PAI) including a group of moderators should alleviate this problem for identifying interactions.

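### The analysis and power sections make no allowance for therapist; if therapists are nested in arm, standard errors for the CBT–PDT contrasts will be too small.

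*Protocol article*

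**What the plan says.** The Statistical analysis plan section of the protocol article defines controlled direct, natural direct and natural indirect effects and then says: "Simple regression models will suffice to estimate the direct and indirect effects above". The qualification that follows concerns confounding between mediator and depression. Moderation is to be estimated by an interaction term in the regression. The longitudinal extensions (marginal structural and structural nested mean models) likewise carry no therapist term.

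The Power analysis section takes as its basis a "t-test comparison of two independent groups (of equal size) as the total effect" and gives "a sample size (each group) of 26 / 64" for 80% power at the 5% level "to detect a difference of a large (0.8) / medium (0.5) effect size, respectively".

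On delivery, the Therapists section says: "The psychotherapy with CBT and PDT are conducted by therapists from Nydalen and Vinderen psychiatric outpatient clinic". It gives neither the number of therapists nor their caseload. It describes their training in the two therapies in words that fit either therapists trained in both or two groups trained in one each. The Common versus specific factors section plans comparisons between arms of Working Alliance Inventory (WAI) scores among improved patients.

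No section mentions a therapist effect, an ICC, a design effect or cluster-robust standard errors.

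**The concern.** In individual psychotherapy, patients of the same therapist may resemble each other in outcome, alliance and mediator change. If each therapist delivers only one of the two therapies, therapist differences sit inside the arm comparison. A regression or t-test that treats patients as independent then understates the standard error of that comparison. The affected contrasts are the total effect, the arm effect on a mediator (the first leg of any indirect effect) and the WAI comparisons.

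The stake is interpretive as well as numerical. The trial sets out to attribute mechanisms to CBT or to PDT and to ask whether alliance works differently in the two. Under nesting, a few unusually strong or weak therapists could show up as a difference between therapies or as a therapy-specific mechanism, with an interval too narrow to warn the reader.

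**Working it through.** **Inputs from the article.** Total sample: "One hundred patients with a diagnosis of MDD will be randomized to either CBT or PDT", taken as 50 per arm because the power text assumes equal groups. Effect sizes 0.8 and 0.5, level 5% (two-sided assumed), power 80%, stated sizes 26 and 64 per group.

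**Inputs assumed, because the article does not give them.** Patients per therapist m = 2.5, 5 or 10 (50/m = 20, 10 or 5 therapists per arm); ICC 0.02, 0.05 or 0.10; therapists nested in arm.

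**Step 1: reproduce the stated sizes.** A two-sided 5% two-sample t-test with 80% power (noncentral t) needs 25.5, so 26, per group at d = 0.8, and 63.8, so 64, at d = 0.5. Both match with independent patients and no clustering allowance. A one-sided test would need 20 and 50 by normal approximation, which does not match.

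**Step 2: power at the planned size under independence.** With 50 per arm and d = 0.5, power is 69.7% by the t-test. By normal approximation it is Φ(0.5 × √(50/2) − 1.96) = Φ(0.54) = 70.5%. The approximation is used below so that the comparisons are like for like.

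**Step 3: effect of nesting.**
- Design effect: DE = 1 + (m − 1) × ICC
- True standard error divided by naive standard error: √DE
- Actual level of the nominal 5% test: 2 × (1 − Φ(1.96/√DE))
- Power at d = 0.5: as in step 2, with 50 replaced by 50/DE

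| m | ICC | DE | SE ratio | Actual level | Power at d = 0.5 |
|---|---|---|---|---|---|
| 2.5 | 0.02 | 1.03 | 1.015 | 5.3% | 69.3% |
| 2.5 | 0.05 | 1.075 | 1.037 | 5.9% | 67.4% |
| 2.5 | 0.10 | 1.15 | 1.072 | 6.8% | 64.5% |
| 5 | 0.02 | 1.08 | 1.039 | 5.9% | 67.2% |
| 5 | 0.05 | 1.20 | 1.095 | 7.4% | 62.6% |
| 5 | 0.10 | 1.40 | 1.183 | 9.8% | 56.1% |
| 10 | 0.02 | 1.18 | 1.086 | 7.1% | 63.4% |
| 10 | 0.05 | 1.45 | 1.204 | 10.4% | 54.6% |
| 10 | 0.10 | 1.90 | 1.378 | 15.5% | 44.2% |

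The middle row worked through: DE = 1 + 4 × 0.05 = 1.20; effective size 50/1.20 = 41.7 per arm; level 2 × (1 − Φ(1.96/1.095)) = 7.4%; power Φ(0.5 × √(41.7/2) − 1.96) = Φ(0.32) = 62.6%. The stated sizes become 26 × 1.20 = 31.2, so 32, and 64 × 1.20 = 76.8, so 77 per group.

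**Step 4: the crossed alternative.** If every therapist treats both arms in balance and there is no therapist-by-treatment variance, the therapist main effect cancels from the arm contrast. The true standard error is then about √(1 − ICC) of the naive one. At ICC 0.05 this is √0.95 = 0.975, and the actual level is 2 × (1 − Φ(1.96/0.975)) = 4.4%, slightly conservative.

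**The case against.** The strongest reply is that the quoted sentence is not about error structure. The section says it is illustrating basic concepts in a simple setting, and the sentence contrasts ordinary regression with the methods needed when a confounder is affected by treatment. A regression with a therapist term is compatible with it. The t-test is a benchmark for sample size and is not named as the analysis. A fuller analysis plan, not shown, could add a therapist term. All of this stands, so the sentence should not be read as a claim that patients are independent. What remains is that the article calls a method sufficient, lists what else is needed without therapist, and reports finished sample sizes that assume independence.

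The second reply concerns facts. A reader might infer that the standard errors are too small as things stand, or that a small set of therapists each carry many patients. The article supports neither. It does not give the number of therapists, their caseload or the ICC, and it leaves open whether a therapist treats in one arm or both. In the balanced crossed case the naive test is about right or slightly conservative. This objection also stands, and it is why the conclusion is conditional.

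Third, the figures concern arm contrasts only. They do not measure any effect on interactions between treatment and patient-level moderators, on mediator–outcome paths or on the Personalized Advantage Index, and nothing is claimed for those here.

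**Conclusion.** The point holds in conditional form. The article calls simple regression sufficient and bases its power figures on independent patients, with no allowance for therapist in a trial of two therapist-delivered treatments. If therapists are nested in arm and the ICC is above zero, arm contrasts on outcome, mediators and alliance will have standard errors that are too small.

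The size depends on assumptions that the article does not settle. With 2.5 patients per therapist the actual level is 5.3–6.8%, close to nominal. With 5 it is 5.9–9.8%, and with 10 it is 7.1–15.5%, each over ICC 0.02 to 0.10. The 15.5% is the worst corner of an assumed grid and should not be quoted as the expected error. In the middle case (5 per therapist, ICC 0.05), power at d = 0.5 falls from about 70% to 63%. If therapists treat both arms in balance, only therapist-by-treatment variance remains a concern.

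**What to change.** 1. State the number of therapists, their expected caseload, and whether each treats in one arm or both.
2. Replace the sentence that simple regression suffices with models that account for therapist and match that structure. If nested: a random therapist intercept with small-sample degrees of freedom. If crossed: therapist and therapist-by-arm terms.
3. For indirect effects and g-estimation, where mixed-model degrees-of-freedom corrections do not carry over, use a therapist-level bootstrap or cluster-robust standard errors with a small-sample correction.
4. Restate power over a range of ICC and caseload, as in the table above.

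The cost is somewhat wider intervals and slightly lower stated power. The change is to the analysis and power text and needs a record of which therapist treated each patient; no new patient assessments are required.

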**Fig. 2 Fig2:**
[figure not shown]
Causal diagram for mediation, A: treatment, M: mediator, Y: outcome and C: measured confounders

Randomization of treatment group also strengthens assessment of effect heterogeneity/moderation, from other variables than the mediator. This is estimated by including an interaction term in the regression.

Direct and indirect effects are generalizable to time-varying mediators, but with similar assumptions as mentioned above. Without time-varying confounders for the mediator—depression relationship that are affected by the group-assignment, the natural direct/indirect effects are identifiable (in addition to the controlled direct effect) in longitudinal equivalents. With a time-varying confounder affected by group-assignment, only the longitudinal equivalent of the controlled direct effect is identifiable, and can be estimated with the marginal structural model [81]. Also, a time-varying moderator effect is identifiable in a structural nested mean model, and can be estimated by g-estimation (Vansteelandt 2016).

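### For a mediator-depression confounder affected by arm, the plan names only the controlled direct effect, which contains no mediated effect, and gives the mediation hypotheses no estimand in that case

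*Protocol article*

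**What the plan says.** Under Mediators of change the protocol asks: "Does improvement occur through different or similar change processes (mechanisms) in the two treatment modalities". It then lists several processes expected to mediate improvement in CBT and several others in PDT.

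The section Statistical analysis plan defines three effects. The natural indirect effect (NIE) carries the mediation content: "effect of treatment group assignment on symptoms of depression that operates by changing the mediator". The controlled direct effect is the change in depression "if the mediator where fixed at level $$m$$ uniformly in the whole population, but the treatment group where changed".

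The natural effects need an extra condition: "no mediator- depression confounder should be affected by treatment group assignment". For the case where it fails, the plan says: "If such an influence (arrow) is plausible, the natural direct and indirect effects are not identifiable. The controlled direct effect can still be identified", by a structural mean model and g-estimation. The paragraph after the Fig. 2 caption repeats this for time-varying mediators: "With a time-varying confounder affected by group-assignment, only the longitudinal equivalent of the controlled direct effect is identifiable", estimated with a marginal structural model. The only other g-estimation target named there is a moderator effect.

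On the arm-by-mediator interaction the plan says: "It can be argued that the interaction term should be included", even when it is not significant.

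**The concern.** Mechanism of change is an overall aim of the trial, and the arms are expected to be equally effective (Aims). The mediated effect therefore carries much of the scientific content. If an arm-affected confounder is present, the plan leaves a direct effect with the mediator held fixed. No value of that quantity, taken alone, supports or refutes improvement through the mediator.

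The case is likely here for three reasons:

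- Many parallel processes are hypothesised to respond to treatment. When one is analysed as the mediator, the others are candidate confounders that arm may affect.
- Under Common versus specific factors, alliance is expected to differ between improved patients of the two arms.
- BDI is measured alongside several candidate mediators (for example DAS, TAS-20 and SIPP-SF) at 8 and 16 (During therapy; Table 1), and the plan intends to use repeated assessments. Earlier BDI can affect both the later mediator and later depression, and arm can affect it.

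The practical risk is that a CDE is reported as the mediation result, or that total effect minus CDE(m) is read as mediation without its condition.

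**Working it through.** The plan gives no figure on this point, so there is none to reproduce. All coefficients below are illustrative assumptions in SD units; none comes from the protocol.

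**Model.** Arm A, arm-affected confounder L, mediator M, depression Y, with reference-arm means of zero:

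- L = g·A + error
- M = b1·A + b2·L + error
- Y = t1·A + t2·M + t3·A·M + t4·L + error

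From these, with D = b1 + b2·g as the total arm difference in M:

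- CDE(m) = t1 + t3·m + t4·g. Neither b1 nor b2 appears.
- Interventional indirect effect = (t2 + t3)·D with the slope of arm a=1, or t2·D with the reference-arm slope. In this linear model the NIE has the same value as the first.
- Total effect = t1 + t4·g + (t2 + t3)·D.
- Total effect minus CDE(m) = (t2 + t3)·D - t3·m.

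**No interaction.** t1 = 0, t2 = 0.4, t3 = 0, t4 = 0.3, g = 0.2, b2 = 0.3. CDE(0) = 0.3 × 0.2 = 0.06.

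| b1 | D | Indirect effect | CDE(0) | Total | Total - CDE |
|---|---|---|---|---|---|
| 0 | 0.06 | 0.4 × 0.06 = 0.024 | 0.06 | 0.084 | 0.024 |
| 0.8 | 0.86 | 0.4 × 0.86 = 0.344 | 0.06 | 0.404 | 0.344 |

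The CDE does not separate the two situations. The difference from the total effect does.

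**Interaction t3 = -0.3, b1 = 0.8.** Total = 0.06 + 0.1 × 0.86 = 0.146.

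| m | CDE(m) | Total - CDE(m) |
|---|---|---|
| -1 | 0.06 + 0.3 = 0.36 | -0.214 |
| 0 | 0.06 | 0.086 |
| +1 | 0.06 - 0.3 = -0.24 | 0.386 |

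The interventional indirect effect is 0.1 × 0.86 = 0.086 with the slope of arm a=1 and 0.4 × 0.86 = 0.344 with the reference-arm slope. The difference matches 0.086 only at m = 0, because the reference-arm mean of M was set to zero.

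**Independent large simulation** (1,000,000 subjects, CDE by sequential g-estimation). Direct arm effect 0.2, A to L 0.5, L to Y 0.4, so CDE(0) = 0.2 + 0.4 × 0.5 = 0.40 in three models. The true NIEs are 0.00, -0.5 × 0.7 = -0.35, and (-0.3 - 0.4) × 0.7 = -0.49. In the third, which has an interaction of -0.4, total minus CDE(m) is -0.49 at m = 0 and -0.09 at m = 1.

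**Simulation at N = 100** (5,000 runs, no interaction). A to L 0.4, A to M 0.5, L to M 0.5, M to Y 0.3, L to Y 0.4. The true indirect effect is 0.3 × (0.5 + 0.5 × 0.4) = 0.21.

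| Residual SDs | Interventional mean (SD) | Ignoring L | Natural-effect formula |
|---|---|---|---|
| All 1 | 0.209 (0.101) | 0.32 | 0.15 |
| M and Y 0.8, L 1 | 0.209 (0.093) | 0.37 | 0.15 |

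Hand check: ignoring L makes the mediator slope 0.3 + 0.4 × 0.5/(0.25 + residual variance of M). That is 0.46 with variance 1 and 0.525 with variance 0.64; times 0.7 gives 0.32 and 0.37. The natural-effect formula gives 0.3 × 0.5 = 0.15. In these runs, total effect minus the g-estimated CDE equalled the interventional estimate to rounding error.

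**The case against.** Three stronger readings are tempting, and the document does not support them.

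- *The plan itself treats arm-affected confounding as plausible.* It does not. Both statements are conditional, and the opposite case is discussed too. Likelihood has to be argued from the hypotheses and the assessment schedule.
- *The mediator question gets no answer.* This goes too far. Randomisation identifies the total effect, and in the linear case without interaction the total minus the g-estimated CDE is exactly the estimator proposed here. G-estimation in that case also produces the confounder-adjusted mediator slope, so the ingredients are at hand.
- *The statement that only the CDE is identifiable is false.* Among the three effects the plan defines, it is correct.

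It can also be said that the section is expository, and that a condensed article may leave further estimands to an analysis plan that is not shown. That is fair. But the article does go into what remains when the condition fails, and what it names there cannot by itself address the stated hypotheses. A fuller plan that repeated this would inherit the gap.

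A further objection is that the hypotheses are posed within each modality, whereas interventional effects compare arms. If both arms move the mediator equally, the interventional indirect effect is near zero even if the mediator drives all improvement. This stands, and it applies equally to the NIE the plan already uses.

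**Conclusion.** The point holds in limited form. For an arm-affected mediator-depression confounder the plan names only CDE(m), which by its own definition excludes the mediated pathway. The available difference from the total effect is neither named nor given its condition. Without interaction that difference suffices. With the interaction the plan leans towards keeping, it depends on m and can change sign: -0.21 to +0.39 in the example, against 0.09 for the interventional indirect effect with the slope of arm a=1.

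The sizes rest on assumed linear models and coefficients, and the -0.3 interaction is an assumption. The structural conclusion, that CDE(m) does not contain the arm's effect on the mediator, follows from the plan's definition alone. Interventional effects need the randomised arm and no unmeasured mediator-outcome confounding given the measured history, essentially what the CDE already requires. The plan should be amended here; the point does not invalidate the trial or its other analyses.

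**What to change.** - For an arm-affected confounder, name the interventional direct and indirect effects as the mediation estimand. Estimate them by the mediational g-formula with bootstrap intervals. In the linear case, report the total arm difference in the mediator times the mediator slope adjusted for the arm-affected confounders, for each arm's slope.
- Keep CDE(m) as a supplement, at stated values of m within the observed range.
- Reword the identifiability sentence so that it reads: of the three effects defined above, only the CDE is identifiable.
- State that interventional effects are population-level (the mediator is drawn from its distribution in an arm), not individual-level mediation. State too that, like the NIE, they are between-arm contrasts and are near zero if both arms move the mediator equally.

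The cost is analysis-plan wording and code, with no new data. The drawback is the weaker, population-level interpretation.
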